## Abstract

**Background:**

A substantial research base documents the benefits of attendance at high-quality early childhood education and care (ECEC) for positive behavioural and learning outcomes. Research has also found that the quality of many young children’s experiences and opportunities in ECEC depends on the skills, dispositions and understandings of the early childhood adult educators. Increasingly, research has shown that the quality of children’s interactions with educators and their peers, more than any other programme feature, influence what children learn and how they feel about learning. Hence, we sought to investigate the extent to which evidence-based professional development (PD) – focussed on promoting *sustained shared thinking* through quality interactions – could improve the quality of ECEC and, as a consequence, child outcomes.

**Methods/design:**

The Fostering Effective Early Learning (FEEL) study is a cluster randomised controlled trial for evaluating the benefits of a professional development (PD) programme for early childhood educators, compared with no extra PD. Ninety long-day care and preschool centres in New South Wales, Australia, will be selected to ensure representation across National Quality Standards (NQS) ratings, location, centre type and socioeconomic areas. Participating centres will be randomly allocated to one of two groups, stratified by centre type and NQS rating: (1) an *intervention* group (45 centres) receiving a PD intervention or (2) a *control* group (45 centres) that continues engaging in typical classroom practice. Randomisation to these groups will occur after the collection of baseline environmental quality ratings. Primary outcomes, at the child level, will be two measures of language development: verbal comprehension and expressive vocabulary. Secondary outcomes at the child level will be measures of early numeracy, social development and self-regulation. Secondary outcomes at the ECEC room level will be measures of environmental quality derived from full-day observations. In all cases, data collectors will be blinded to group allocation.

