### Outcome measures and procedures

All measures will be administered at baseline and again after the 9-month intervention period (post-test). The battery of child measures was selected to include outcomes that are important for school readiness (i.e. literacy, numeracy, self-regulation, social development). Such outcomes have also been established by previous research as having a foundational role in child development. In total, the child outcome measurements involve 40–50 min of direct assessment per child (split into two sessions) and 10 min of educator time per child (i.e. approximately 3.3 h of educator time per centre) at each data collection time point. In all cases, child assessments will be carried out by a trained fieldworker in a quiet area of the child’s ECEC centre. All environmental quality ratings will also be conducted by highly trained observers through a 1-day observation of each preschool room in participating centres. All observers will need to achieve a rigorous standard of inter-rater reliability with a highly experienced trainer/observer, as indexed by: an intra-class correlation in ratings > .70; a mean difference in ratings < .75; and at least 80% of item ratings within 1 point. In all cases, the researchers involved in collecting baseline and outcome data will be blinded to each centre’s group allocation.

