Primary child-level outcomes consist of measures of children’s language development: verbal comprehension and expressive vocabulary. Specifically, the Verbal Comprehension subtest of the Differential Ability Scales (retest reliability 0.82; concurrent validity 0.70) [32] is a measure of the receptive language (comprehension) ability of the child, and takes 10–15 min to administer. The Expressive Vocabulary test from the Early Years Toolbox (internal consistency 0.92; concurrent validity 0.60) [33] is an assessment of expressive vocabulary to complement the receptive language measure, and takes 5 min to administer. Secondary outcomes at the child level involve measures of early numeracy, social development and self-regulation. The Early Number Concepts subscale of the Differential Ability Scales (internal consistency 0.89; concurrent validity 0.71) [32] and the Early Numeracy Assessment [34] include numeric concepts of counting, cardinality, number comparison and number combinations (internal consistency 0.74 to 0.79; concurrent validity 0.35 to 0.66). These two assessments each take 10–15 min to complete. The educator-report Child Self-regulation and Behaviour Questionnaire (CSBQ) [33] and Strengths & Difficulties Questionnaire (SDQ) [35] yield subscales of cognitive, emotional and behavioural self-regulation, antisocial and prosocial behaviours, sociability and anxiety/internalising, among others. The CSBQ subscales have internal consistency ranging from 0.74 to 0.89, and concurrent validity in the range of 0.48 to 0.81 [33]. The SDQ subscales have internal consistency in the range of 0.65 to 0.85, and concurrent validity in the range 0.87 to 0.92 [36].

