### Ethical and research governance approval

The study was granted ethical approval by the University of Wollongong Human Research Ethics Committee Social Sciences (HE15/309) on 8 September 2015. Written consent will be obtained from centre directors (for participation and centre observations), educators (who will complete educator-report measures), and children’s parent(s) or legal guardian(s) as a condition for participation. This will include consent for publication of the study results in anonymised aggregate format. As per Consolidated Standards of Reporting Trials (CONSORT) guidelines, the study’s final reporting will follow the CONSORT Statement and its relevant extensions (e.g. cluster trials, nonpharmacological interventions).

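### Blinding is claimed without exception, but the only social-development and self-regulation measures (CSBQ, SDQ) are completed by unblinded centre educators

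*Protocol article*

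**What the plan says.** Three statements carry no exception:

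- Abstract, Methods/design, directly after the list of primary and secondary outcomes: "In all cases, data collectors will be blinded to group allocation".
- Outcome measures and procedures, on who assesses the children: "In all cases, child assessments will be carried out by a trained fieldworker in a quiet area of the child’s ECEC centre".
- The same section, on blinding: "In all cases, the researchers involved in collecting baseline and outcome data will be blinded to each centre’s group allocation".

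On the outcomes, that section says: "Secondary outcomes at the child level involve measures of early numeracy, social development and self-regulation". Numeracy has two directly administered tests. For the other two domains the text reads: "The educator-report Child Self-regulation and Behaviour Questionnaire (CSBQ) [33] and Strengths & Difficulties Questionnaire (SDQ) [35] yield subscales of cognitive, emotional and behavioural self-regulation". No other instrument is named for them, and Table 1 lists the SDQ and CSBQ under child assessments. The section on ethical approval confirms who fills them in: "educators (who will complete educator-report measures".

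The PD is aimed at early childhood educators, and the comparator is usual practice with no extra PD. The Professional development intervention section gives self-regulation as one of eight core content areas. Phase 3 opens the online material to all staff of a centre, including those who do not attend the face-to-face sessions.

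**The concern.** For the CSBQ and SDQ the person who produces the score is the educator. Blinding whoever hands out or gathers the form does not blind the person who completes it. With no sham programme in the control arm, educators in an intervention centre cannot be kept unaware of allocation. The programme also addresses one of the constructs they rate, so it may change the standard against which they judge children even if the children do not change.

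At stake is the reading of two of the three secondary child domains. The Aims section hypothesises a positive effect on the identified child outcomes and on room quality, and says that support for this would be evidence that better practice mediates child outcomes. A difference on the CSBQ or SDQ could enter that argument under a blinding statement that does not hold for it.

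**Working it through.** The point turns on reading sections against each other. No figure in the plan is disputed.

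**Step 1: who produces each outcome.**

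| Outcome | Produced by | Does the blinding claim fit? |
|---|---|---|
| Verbal comprehension, expressive vocabulary (primary) | Fieldworker, direct test | Yes |
| Early number concepts, early numeracy (secondary) | Fieldworker, direct test | Yes |
| ECERS-E, SSTEW (secondary, room level) | Trained observer | Yes |
| CSBQ, SDQ (secondary: social development, self-regulation) | Centre educator | No |

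The claim fails for one row, which holds two of the three secondary child domains.

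**Step 2: does the planned analysis remove the problem?** Statistical analyses and power regresses post-test on baseline and group. If educators in one arm shift their rating standard by *b* between the two occasions, the expected group coefficient is the true effect plus *b*. Baseline adjustment removes differences already present at baseline, not one that arises afterwards. Baseline ratings may not be wholly free of influence either: under Study design they follow allocation, and Trial status reports that PD had started while child pretests were unfinished.

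**Step 3: illustration of size.** The value of *b* is an assumption, since the document gives none.

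The plan's own figure is reproduced first. With 90 × 13 = 1170 children, 585 per arm, independence and 80% power:

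- two-sided 5%: (1.960 + 0.842) × √(2/585) = 0.164 SD (plan: 0.16)
- two-sided 1%: (2.576 + 0.842) × √(2/585) = 0.200 SD (plan: 0.20)

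The clustered range of 0.17 to 0.20 SD corresponds to a design effect 1 + 12 × ICC with an ICC of roughly 0.01 to 0.04.

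The standard error implied by a detectable effect *D* is *D*/(1.960 + 0.842), which is 0.17/2.802 = 0.061 or 0.20/2.802 = 0.071. With no true effect, the probability of a nominally significant result is 1 − Φ(1.960 − *b*/SE) + Φ(−1.960 − *b*/SE):

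| Assumed shift *b* (SD) | *D* = 0.20 | *D* = 0.17 |
|---|---|---|
| 0 | 5.0% | 5.0% |
| 0.05 | 10.8% | 13.1% |
| 0.10 | 28.8% | 37.8% |
| 0.15 | 55.6% | 69.6% |

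These figures apply to one outcome tested alone and take the plan's implied standard errors to hold for the CSBQ and SDQ. If ratings by a shared educator correlate more strongly within centres than the plan implies, the standard error is larger and the probabilities are lower.

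**The case against.** The strongest reply is that this is loose wording, not a hidden flaw. The methods label the questionnaires as educator-report, budget educator time for them and say who completes them. The methods sentence on blinding speaks of researchers, and educators are not researchers, so it can be literally true. The fieldworker sentence might likewise be meant for direct testing only. These outcomes are already secondary, educator report is an ordinary way to measure these domains, and final reporting is committed to CONSORT and its extensions.

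Much of this stands: the document does not conceal who rates. But none of it rescues the abstract, which refers to data collectors and follows a list that includes both domains. The fieldworker sentence also sits badly with Table 1, which counts both questionnaires as child assessments. An analysis plan that is not shown cannot make the article's blanket statement true.

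A reader might infer more than the text supports:

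- *That every rating educator in the intervention arm received the PD.* The document does not say which educators fill in the forms. It separates staff who attend the face-to-face phases from others who have online access, and it expects incomplete uptake. What it supports is that raters work in centres offered the PD.
- *That the bias is as large as the detectable effect of 0.17 to 0.20 SD.* Nothing in the document gives a size. Setting the shift equal to the detectable effect returns 80% by the definition of power and shows nothing further.
- *That the results will be reported as blinded at rater level.* The document does not say so.

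**Conclusion.** The concern holds in a limited form. The abstract's blinding statement is untrue for the CSBQ and SDQ, and the fieldworker statement in the methods does not fit them. Effects on social development and self-regulation are therefore open to rating bias of unknown direction, which could create an apparent benefit or mask a real one. On their own they are not blinded evidence of benefit.

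This rests on the educators' role as stated in the article and on the inference that staff of a centre offered the PD know its allocation. The 11% to 70% range is conditional on an assumed shift of 0.05 to 0.15 SD and is not an estimate of the bias in this trial. It would be wrong to extend the point to the primary language outcomes, the numeracy tests or the room observations, since all of these come from fieldworkers or observers stated to be blinded.

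**What to change.** 1. In the abstract and in Outcome measures and procedures, limit the blinding and fieldworker statements to the directly administered language and numeracy tests and to the observer ratings.
2. State in the same places that the CSBQ and SDQ are completed by centre educators who are not blinded.
3. Say that effects on these two questionnaires will be interpreted as open to rating bias in either direction, and will not by themselves be presented as blinded evidence of benefit.
4. Optionally, record who rated each child and that person's PD attendance, and add a sensitivity analysis by rater exposure or by whether the same educator rated on both occasions.

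A random effect for rater is not a remedy: it models correlation between ratings and leaves a systematic shift between arms in place.

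Items 1 to 3 cost a few sentences and a more modest claim on two secondary domains. Item 4 adds a rater identifier and an attendance field. No change to the design, the sample size or the primary analysis is needed.

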**Discussion:**

This is the first randomised controlled trial of a new approach to PD, which is focussed on activities previously found to be influential in children’s early language, numeracy, social and self-regulatory development. Results should inform practitioners, policy-makers and families of the value of specific professional development for early childhood educators.

**Trial registration:**

Australian New Zealand Clinical Trials Registry (ACTRN) identifier ACTRN12616000536460. Registered on 27 April 2016. This trial was retrospectively registered, given the first participant (centre) had been enrolled at the time of registration.

**Electronic supplementary material:**

The online version of this article (doi:10.1186/s13063-016-1742-1) contains supplementary material, which is available to authorized users.

## Background

There is widespread consensus that attendance in early childhood education and care (ECEC) is likely to confer a benefit on children [1]. Nonparticipation in ECEC programmes places children at a developmental disadvantage both academically and socially [2, 3]. Furthermore, national surveys [4] and longitudinal research [5] show the enduring benefits that *high-quality* ECEC provides into adolescence and beyond [1]. Indeed, there is strong evidence from independent sources that the benefits of ECEC are moderated by the quality of provision [1].

Recent initiatives in Australia have begun to recognise the short- and long-term benefits of investing in ECEC. The National Quality Framework (NQF) and Early Years Learning Framework (EYLF) [6, 7], for instance, have identified structural and process quality indicators that are important for enhancing child outcomes. These state and national initiatives include measures to improve adult-to-child ratios, introduction of minimum qualifications, regulation based on nationally recognised standards of practice and improvements in curriculum and reporting requirements. This implementation of nationally consistent quality standards is a significant transformation, and a move toward ensuring high-quality educational experiences for children and workforce professionalisation.

In recognition of the important role that ECEC plays in the lives of young children, the New South Wales (NSW) Government has introduced initiatives to ensure that all children have universal access to early education in the year before formal schooling, which starts at 5 years of age. Over recent years, the number of children participating in ECEC services across Australia has increased by 39.5% from 2004 to 2012 [8, 9].

While ECEC attendance in NSW is moving toward a universal provision, there remain questions about the prevalence of high-quality ECEC. Recently, positive long-term associations were documented between ECEC attendance and a range of learning outcomes in national assessments at 8 years of age (i.e. numeracy, reading and spelling) [10]. However, closer inspection of these results showed that the greatest benefits were for children whose preschool teacher held a degree or diploma qualification [10]. Consistent with such findings, the Early Years Workforce Strategy 2012–2016 recognises the importance of a skilled workforce in ensuring ‘the delivery of high-quality ECEC services’ [11]. Nevertheless, the Australian ECEC context continues to be plagued by significant variations in educators’ qualifications. As of January 2014, only ECEC centres with more than 25 places are required to have a full-time, degree-qualified educator. A further 50% of staff needs to be working toward a diploma-level qualification, with the remainder only holding basic certification.

Given this variability in ECEC educators’ training, alternative models, such as ongoing professional development (PD), need to be examined for increasing pedagogical knowledge and improving quality in early childhood educational practice. Increasing child participation in ECEC means that the quality of many young children’s experiences and opportunities depends on the skills, dispositions and understandings of the adult ECEC workforce [12–15].

### The quality of ECEC, child outcomes and professional development

The quality of ECEC is multidimensional, encompassing the physical ECEC environment, the educational curriculum, staff training and qualifications, child-staff ratios, group sizes, staff turnover and interpersonal relationships. Yet, many studies have been discrepant in their conceptualisation of quality and its impact on children’s outcomes. Recent large-scale literature reviews by Melhuish et al. [3] and Siraj and Kingston [16] have concluded, based on international evidence, that the following characteristics of ECEC quality are particularly important for enhancing children’s development:Adult-child interaction that is responsive, affectionate and readily availableWell-trained staff who are committed to their work with childrenA developmentally appropriate curriculum with educational contentRatios and group sizes that allow staff to interact appropriately with childrenSupervision that maintains consistency in the quality of careStaff development that ensures continuity, stability and improving qualityFacilities that are safe, sanitary and accessible to parentsWorking with families, sharing educational goals and supporting early home learning environments

Many studies have recognised that while physical resources are necessary for quality ECEC, the most important ingredient for quality provision is the quality of the staff who work with the children and families [17]. Cooke and Lawson [18] reported that improving the quality of ECEC and learning outcomes for children required a highly skilled workforce. Increasingly, research has shown that some of the strongest predictors of child outcomes pertained to the quality of adult-child and child-child interactions. Children’s interactions with educators and their peers, more than any other programme feature, are seen as determining what the children learn and how they feel about learning [13, 19–21].

A review and meta-analysis [22] concludes that there is ample evidence that providing sector-specific qualifications and PD for educators improves children’s learning and wellbeing. Evidence has also accrued on the particular value of interactions supporting *sustained shared thinking* (SST). The term sustained shared thinking was originally coined from research considering components of excellent practice in the Effective Provision of Preschool Education (EPPE) study in England [23]. Since this pioneering study, SST has been widely used in many Early Years Frameworks across the world. The EPPE project’s findings, including SST, influenced development of the Australian EYLF [24], as well as England’s Early Years Foundation Stage [25]. However, the practices associated with SST have been found lacking in many ECEC settings [13, 20, 23, 26]. Hence, there is a need to develop staff capacity for fostering interactions that contain SST, as well as other types of interaction that similarly foster language development, critical thinking, self-regulation and social development.

In line with this thinking, a PD programme has been developed that specifically addresses, among other things, the enhancement of staff interactions with children in ways that the available evidence suggests should foster children’s development, especially in the areas of language development, self-regulation, early numeracy and social development. These child outcomes are particularly important because they have been consistently linked to children’s longer-term development in terms of educational achievement and social adjustment in Australia [27, 28], the UK [29], USA [30] and China [31].

### Aims of the study

The main objective of this study is to evaluate whether a PD programme seeking to enhance the quality of ECEC interactions, compared to routine practice, can enhance ECEC quality and child outcomes. The primary outcomes at the child level will be two measures of language development – verbal comprehension and naming vocabulary – as these may be particularly sensitive to environmental changes that may occur from the PD programme [1]. Secondary outcomes at the child level will include other central aspects of child development, notably early numeracy, social development and self-regulation. Secondary outcomes at the centre level will be changes in two environmental rating scales focussing on: (1) curriculum content, concept development and pedagogy and (2) interactional quality through relational and intentional pedagogy. It is hypothesised that the PD intervention will have a positive effect on the identified child outcomes and ECEC room-level environmental quality ratings. If supported, this would provide evidence that improvements in professional practice are mediating child outcomes.

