## Methods/design

### Study design

The study employs a clustered randomised controlled trial design. Ninety ECEC centres in NSW, Australia, will be recruited to ensure representation across National Quality Standards (NQS) ratings (Working Towards, Meeting, Exceeding), location (metro, regional), centre type (long-day care and preschool) and socioeconomic areas (as based on the Socio-Economic Indexes for Australia; SEIFA). The sample will ensure representation across these variables, but is not intended to be fully representative of the population (see ‘Centre characteristics and recruitment’ section below). Stratified random assignment of centres to control and intervention groups will occur after the collection of baseline environmental ratings. Once collected, participating centres will then be stratified by centre type and NQS rating and randomly allocated to one of two groups: (1) the *intervention* group (*n* = 45 centres) receiving the PD intervention or (2) the *control* group (*n* = 45 centres) that will continue engaging in typical classroom practice. Fieldworkers, blinded to group allocation, will then conduct baseline child assessments early in the following year. The 9-month PD intervention will occur throughout much of 2016. Post-intervention child assessments and environmental quality ratings will occur again in late-2016 to evaluate any changes as a result of the intervention, relative to control. A flowchart depicting the sequence of recruitment, intervention and assessment for FEEL is shown in Fig. 1. An outline of Standard Protocol Items: Recommendations for Interventional Trials (SPIRIT) time points and actions for the FEEL study is shown in Table 1 (see Additional file 1 for the trial’s SPIRIT Checklist).

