The effect of the PD intervention will be considered in two ways. Firstly, we will compare 45 intervention and 45 control centres for environmental quality in order to estimate the effect upon staff behaviour in the centres. ECEC room-level outcomes will be analysed using linear regression models with post-test outcomes as dependent variables and baseline measures as independent variables. Child-level data analyses will control for clustering within centres using multilevel models (hierarchical models or random-effect models), which can account for clustering of repeated assessments within individuals and clustering of individuals within centres. Post-test scores for primary and secondary outcomes will be used as dependent variables, with baselines variables and group membership as independent variables. Multiple imputation methods will be used for missing individual outcome data. If data are normally distributed we will fit linear models. If not, we will categorise outcome data and use longitudinal logistic regression to evaluate the differences between intervention and control groups. Sensitivity analyses will be conducted for all primary and secondary outcomes. Inverse probability weighting will be considered if missing data are more prevalent than expected and/or there is differential attrition between trial arms. Additionally, reasons for the differential attrition will be fully explored. Secondary analyses from explicit hypotheses (e.g. subgroup, including level of deprivation) will be specified in advance in a statistical analysis plan.

In applying power calculations, we took into account that children are clustered in centres.

Conservative power estimates, after adjusting for the clustered (nested) design, indicate that we can detect an effect size as low as 0.17 standard deviation (SD) units with 80% power for all child outcomes. This is based on a conservative estimate of 13 children per centre, yielding an estimated sample size of 1170. For continuous outcomes, these correspond to differences between the means in the treatment and control groups in units of the SD.

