## Discussion

The study is dependent upon the cooperation of the centres recruited to the study, the staff within those centres and the parents of the children in those centres. Hence, substantial efforts have been expended in producing information leaflets for all concerned to explain the study, its aims and the potential benefits of the study for ECEC centres in the future and the children who will use them. A substantial amount of time has been required for meetings and other liaison between the research team and potential centres for recruitment. Thus far, we believe that the necessary groundwork has been made and hope that the study will proceed according to plan. This would mean that the next publication regarding this trial will concern its results, indicating whether there is an impact of the PD programme on child outcomes as a consequence of improved centre staff practice and pedagogy.

While the FEEL study was designed to yield the strongest possible evidence of intervention efficacy, the study is limited in its focus on intervention evaluation and does not, at present, include further qualitative evaluation (e.g. case studies of centres with the greatest and least change, process evaluation, analysis of PD participants’ feedback and comments). This is due to constraints of the available funding, but could be added should funding become available for these important follow-on investigations. Even in lieu of these additions, the results of the FEEL study should inform decision-making about future practice and policy regarding the provision of evidence-based PD to ECEC staff, as well as potentially informing the content of staff training. Such an impact would be of benefit to ECEC centres and their staff, as well as the communities, families and children who utilise these centres.

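### Positive effects on both room quality and child outcomes would be consistent with mediation through improved practice, but the two arm comparisons described cannot by themselves show it

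*Protocol article*

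**What the plan says.** The Aims of the study section sets out a two-part hypothesis: "It is hypothesised that the PD intervention will have a positive effect on the identified child outcomes and ECEC room-level environmental quality ratings". The next sentence draws the inference: "If supported, this would provide evidence that improvements in professional practice are mediating child outcomes". The Discussion expects the results paper to report in the same terms, "indicating whether there is an impact of the PD programme on child outcomes as a consequence of improved centre staff practice and pedagogy".

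The Statistical analyses and power section describes two analyses.

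- **Room level:** "we will compare 45 intervention and 45 control centres for environmental quality". The model is given as follows: "ECEC room-level outcomes will be analysed using linear regression models with post-test outcomes as dependent variables and baseline measures as independent variables".
- **Child level:** multilevel models, for which the text says: "Post-test scores for primary and secondary outcomes will be used as dependent variables, with baselines variables and group membership as independent variables". Post-test room quality is not among the listed predictors.

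On timing, the Study design section says: "Post-intervention child assessments and environmental quality ratings will occur again in late-2016".

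**The concern.** Mediation has two links: PD changes practice, and the change in practice changes the child's score. The room-level comparison addresses the first link. The child-level comparison gives the total effect of PD on children. Neither addresses the second link. Two positive results fit a chain from PD through room quality to the child, and they fit equally well two effects that arise side by side.

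Two design features make the gap harder to close. The ratings and the child scores are post-tested in the same period, so their order in time is not established. Randomisation protects the comparison of arms, but not the relation between room quality and child scores within arms, which other centre characteristics can confound.

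The Discussion says the results should inform decisions on practice and policy. A statement about the pathway would tell policy-makers that raising measured room quality is what helps children, which is a different claim from saying that the programme helps children.

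**Working it through.** **Inputs from the Statistical analyses and power section.** 45 versus 45 centres; 13 children per centre, 1170 in all, so 585 per arm; 80% power; detectable child effect 0.17 to 0.20 SD at p < .05 (0.16 SD if children were independent); room-level effect 0.60 SD.

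**Assumptions.** Two-sided 5% tests (sidedness is not stated); one room scale and one child outcome; no baseline adjustment; room and child errors independent given arm. The ICC is not stated and is inferred in step 1.

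**Step 1: reproduce the plan's figures.** The detectable effect is (1.960 + 0.842) × √(2/n per arm), with 2/n multiplied by 1 + 12 × ICC for clustered children.

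- Independent children: 2.802 × √(2/585) = 0.164 (stated 0.16).
- Clustered children: 0.17 implies ICC = [(0.17/0.1638)² − 1]/12 = 0.006; 0.20 implies [(0.20/0.1638)² − 1]/12 = 0.041.
- Room level: 2.802 × √(2/45) = 0.591 (stated 0.60).

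The stated figures reproduce, and 0.60 SD behaves as an effect detectable with about 80% power.

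**Step 2: how often are both results positive when nothing is mediated?** Suppose PD has a true effect on room ratings and a true effect on children, but measured room quality has no effect on children. With independent errors, the chance that both comparisons are significant in favour of PD is the product of the two powers, each Φ(effect/SE − 1.960).

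- Room, 0.60 SD: SE = √(2/45) = 0.2108; Φ(2.846 − 1.960) = 0.812.
- Child, 0.20 SD, ICC 0.041: SE = √(2/585 × 1.492) = 0.0714; Φ(2.800 − 1.960) = 0.800.
- Product: 0.812 × 0.800 = 0.650.

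| Room effect (SD) | Child effect (SD) | ICC | Room power | Child power | Both positive |
|---|---|---|---|---|---|
| 0.60 | 0.20 | 0.041 | 0.812 | 0.800 | 65% |
| 0.60 | 0.17 | 0.0064 | 0.812 | 0.800 | 65% |
| 0.60 | 0.20 | 0.10 | 0.812 | 0.635 | 52% |
| 0.40 | 0.10 | 0.041 | 0.475 | 0.288 | 14% |
| 0.80 | 0.25 | 0.041 | 0.967 | 0.938 | 91% |
| 0.60 | 0 | 0.041 | 0.812 | 0.025 | 2% |
| 0 | 0.20 | 0.041 | 0.025 | 0.800 | 2% |
| 0 | 0 | any | 0.025 | 0.025 | 0.06% |

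**Step 3: check by simulation.** With 20,000 trials per scenario and t tests on centre means, the first two rows gave 63.5% and 63.4%, and the 0.80/0.25 row gave 90.1%. The rows with only a room effect and with no effect gave 2.0% and 0.06%.

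**Step 4: what the missing link adds.** In the simulated trials of the first two rows, a criterion that also required a significant relation between room rating and child score, adjusted for arm, was met in 2.2% and 2.0%. This comparison assumes no confounding of that relation, which randomising PD does not guarantee.

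**The case against.** The sentence sits in the aims, and its wording is soft: it speaks of providing evidence. No test or criterion in the statistical section depends on it, and the Discussion passage expresses an expectation about a later paper. A reader might infer that the plan contains a decision rule that declares mediation whenever both results are positive. The document does not support that reading. It does not define when the hypothesis counts as supported, and if every outcome named had to be positive, the joint probability would be lower than the one calculated here.

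The protocol also speaks of professional practice, not of scores on the two rating scales. PD is given only to staff, so an effect on directly assessed children would presumably pass through something staff do differently. Even the home-learning content is taught to staff. This stands. The zero-mediation scenario concerns measured room quality; it would be wrong to infer that the child effect could plausibly bypass staff practice altogether. An effect on the mediator is also necessary for mediation, so the room result is relevant to it.

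Finally, the article defers pre-specified secondary analyses to a statistical analysis plan that is not at hand, and a mediation model may be there. Its absence from the article is therefore not the fault. The fault is the inference as printed, which rests on the two effects alone and does not become valid through an analysis described elsewhere.

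**Conclusion.** The point holds as one about interpretation. Effects on both room quality and child outcomes would be compatible with mediation, but the comparisons described cannot distinguish it from parallel effects.

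The 64-65% is the joint power of the two comparisons when both effects are real and mediation through measured room quality is exactly zero. It is not the chance that this trial will reach a false conclusion, and it should not be quoted without that condition and its range. It depends on the assumed effects and ICC, and on the simplifications listed in the check. It grows with power, so a larger trial would not cure the problem.

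The randomised comparisons, the primary outcomes and the sample size are untouched. Whether PD improves child outcomes is answered by the intention-to-treat contrast, whatever the pathway.

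**What to change.** Reword the sentence in the aims to say that effects on both would be consistent with, but would not by themselves show, mediation through improved practice. Reword the matching sentence in the Discussion so that it promises the effect on children and the effect on practice, without making one the consequence of the other.

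If a pathway claim is wanted, base it on a pre-specified secondary multilevel mediation analysis: group to centre post-test rating to child post-test score, adjusted for baseline rating, baseline child score and the stratification factors (centre type and NQS rating). Report an interval for the indirect effect and a sensitivity analysis for unmeasured confounding between rating and child score. Because both are post-tested in late 2016, the report should also say that their time order is assumed. If the statistical analysis plan already contains such an analysis, a cross-reference is enough.

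The cost is a weaker stated claim, or a modest extra analysis of data already being collected.
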